# REACT SHOCK trial protocol and analysis plan—a multicenter randomised controlled trial comparing individualised blood pressure target versus standard blood pressure target among critically ill patients with shock

**DOI:** 10.1186/s13063-025-09142-9

**Published:** 2025-10-14

**Keywords:** Critical illness, Shock, Blood pressure targets, Relative hypotension, Randomised clinical trial, Mortality, Protocol, Statistics

## Abstract

**Background:**

Critically ill patients with shock receiving vasopressor or inotrope therapy in ICU are often exposed to relative hypotension, which is quantified as percentage blood pressure deficit relative to usual pre-illness blood pressure. Whether minimising such blood pressure deficit, by adjusting blood pressure targets according to patients’ pre-illness blood pressure (individualised blood pressure target strategy), can improve clinical outcomes remains unclear. Therefore, we are conducting a multicenter randomised controlled trial, the REACT SHOCK RCT, comparing individualised blood pressure targets to standard care among critically ill patients with shock.

**Methods:**

The REACT SHOCK RCT is an international, multicenter, parallel-group, randomised, standard-care controlled, clinical superiority trial that will be conducted in up to 35 ICUs in Australia, Ireland, Singapore, UK and USA. In total, 1260 patients, receiving vasopressor therapy for non-haemorrhagic shock in ICU, will be randomly assigned to individualised mean arterial blood pressure (MAP) targets (determined as an average of 2–5 recent pre-illness blood pressure readings within last 3 years, with a MAP target range of 55 to 95 mmHg) or standard care (default MAP target of 65 mmHg) in a 1:1 ratio. The REACT SHOCK RCT is anticipated to complete recruitment by 2028. The primary endpoint is all-cause 14-day mortality. Secondary endpoints are major adverse kidney events by day 14, all-cause 90-day mortality, survival time to 14 days and 90 days, and renal replacement therapy free days by day 28.

**Discussion:**

The REACT SHOCK RCT is the first international multicenter randomised clinical trial designed to ascertain whether an individualised blood pressure target strategy is superior to standard care for critically ill patients with shock. This trial will generate evidence that may influence current recommendations for MAP targets during management of shock in ICU. The pre-specified protocol summary and statistical analysis plan are presented here.

**Trial registration:**

Prospectively registered on Australian and New Zealand Clinical Trials Registry (ANZCTRN 12623000044628); ClinicalTrials.gov ID NCT05850962 dated 29th April 2023.

**Supplementary Information:**

The online version contains supplementary material available at 10.1186/s13063-025-09142-9.

## Introduction

### Background and rationale

Targeting an adequate mean arterial blood pressure (MAP) with the aid of vasopressors and/or inotropes is one of the fundamental tenets of management of shock in ICU. Although current guidelines strongly recommend a target MAP of 65 mmHg [1–4], it is unclear whether this is the optimal MAP target for each individual patient. Optimal MAP targets may differ among individuals either due to differences in usual pre-illness blood pressure for each individual, different states of tissue autoregulation capacity during critical illness, or other potential unknown reasons for individual variability, possibly including genetic factors [5]. Indeed, blood pressure management to prevent or mitigate new onset organ dysfunction is a priority for future research [6].

In real-world practice, critically ill patients with shock receiving vasopressor or inotrope therapy in ICU are often exposed to a degree of MAP-deficit relative to their usual pre-illness MAP [7]. Recently, we conducted a multicenter prospective cohort study that demonstrated an independent association between time-weighted average MAP-deficit during vasopressor support and subsequent adverse clinical outcomes including 14-day mortality and major adverse kidney events (MAKE-14) [8]. This study highlighted that ICU patients experience near-universal MAP-deficit despite near-perfect maintenance of target MAP of at least 65 mmHg [9]. Additionally, the MAP-deficit was positively associated with 14-day mortality and MAKE-14, suggesting that MAP-deficit could be a more relevant target for haemodynamic management among patients with shock than pursuing a standard MAP threshold of 65 mmHg [3, 4, 8]. Whether minimising such MAP deficit, by adjusting blood pressure targets according to patients’ pre-illness blood pressure (individualised blood pressure management strategy), can improve clinical outcomes remains unknown. On the one hand, individualised MAP target may offer benefit by aligning treatment with the patient’s usual physiological baseline, potentially reducing the risk of organ hypoperfusion, but it may also result in increased vasopressor use. On the other hand, standard MAP target could reduce vasopressor exposure but may also fail to adequately support organ perfusion in patients with higher baseline blood pressure.

Accordingly, we are conducting a multicenter randomised controlled trial (REACT SHOCK RCT; ClinicalTrials.gov ID: NCT05850962) comparing individualised blood pressure target strategy to standard care during vasopressor support among critically ill patients with shock. Our *hypothesis* is that targeting a patient’s pre-illness MAP during management of shock can minimise the degree of MAP-deficit (a measure of relative hypotension), which may help reduce the risk of 14-day mortality and major adverse kidney events in ICU.

### Objectives

The aim of the REACT SHOCK RCT is to determine effectiveness and safety of a strategy, where MAP target during vasopressor therapy for shock in ICU is individualised based on patient’s own pre-illness MAP that would be derived as an average of up to five (and at least two) most recent pre-illness blood pressure readings from within the last 3 years. Our primary objective is to determine whether an individualised MAP target strategy can improve 14-day all-cause mortality compared to standard blood pressure targets among patients with shock. Secondary objectives are to determine whether individualised MAP targets can improve 90-day all-cause mortality, major adverse kidney events by day 14 (MAKE-14), time to death from randomisation to day 14 and day 90, peak increase in serum creatinine, and days alive and free of renal replacement therapy (RRT) by day 28. Safety will be assessed by comparing new adverse events between the two groups.

## Methods: participants, interventions and outcomes

### Trial design and study setting

The REACT SHOCK RCT is an investigator-initiated, pragmatic, international, multicenter, open-label, parallel-group, randomised, standard-care controlled, clinical superiority trial among 1260 critically ill patients, who will be recruited at up to 35 ICUs in Australia, Ireland, Singapore, UK and USA. The trial will be conducted in accordance with Good Clinical Practice guidelines and comply with the principles of the Declaration of Helsinki, national and international regulatory requirements and general data protection regulations. The study is prospectively registered in public registries (ANZCTRN 12623000044628; ClinicalTrials.gov ID NCT05850962) and a pre-specified statistical analysis plan is published here.

### Eligibility criteria

The target population for this trial will comprise ICU patients who satisfy the following criteria and for whom clinicians have an equipoise regarding the target range for optimal blood pressure.

#### Inclusion criteria

Age ≥ 40 yearsSuspected shock state, defined as clinician-initiated vasopressor/inotropic therapy AND supported by any of the following within the last 24 h:Lactate ≥ 2 mmol/l or base deficit ≥ 3 mmol/l,Urine output ≤ 0.5 ml/kg/h or < 40 ml/h for 2 or more consecutive hoursRespiratory rate > 22 per minuteAltered mentation (Glasgow Coma Score < 14)

#### Exclusion criteria

Moribund state or documented not-for-resuscitation ordersReceiving or imminently needing RRTIncrease in serum creatinine of more than 350 μmol/l from the baseline levelEnd stage renal diseaseAt least 24 h have lapsed from the time of initiation of vasopressor or inotropic supportTrauma is the main reason for the current ICU admissionPregnancy, if knownActive bleeding (clinical suspicion or ≥ 3 packed red blood cells within 24 h)Less than two pre-illness blood pressure readings are available from anytime within the last 3 years.Patients on extracorporeal support (ECMO, IABP, VAD)Potential contraindications to either higher or lower blood pressure targets (including but not limited to)Cerebral perfusion pressure guided therapy (e.g. intracranial haemorrhage or subarachnoid haemorrhage or traumatic brain injury)Abdominal perfusion pressure guided therapyAortic injury (e.g. dissection or post-operative)Post cardiac surgeryAny other condition requiring higher or lower blood pressure target specifically.Previously enrolled in REACT SHOCK RCT

### Informed consent

Trained research coordinators or medical doctors at participating ICUs will manually screen patients for eligibility. After determination of eligibility, written informed consent will be obtained from either patients or their legal surrogates.

### Randomisation

Randomisation will be undertaken centrally in a concealed fashion, with a unique computer-generated, site stratified, permuted block randomisation method with random block sizes of 4 and 6. Enrolled patients will be randomly allocated in a 1:1 ratio to either standard care arm or intervention arm.

### Explanation for the choice of comparator

Current guidelines strongly recommend a target mean arterial blood pressure (MAP) of 65 mmHg over higher MAP targets for critically ill patients with shock [1–4]. Therefore, the comparator or the control group will be comprised of patients assigned to standard care that will reflect real-world practice, where vasopressor support is titrated to maintain a default MAP of 65 mmHg unless the treating clinician considers a different MAP target as more appropriate.

### Intervention description

The intervention strategy is to aim for individualised MAP targets that will approximate each individual patient’s usual pre-illness MAP (derived from participant’s own pre-illness MAP based on an average of up to five (at least two) recent pre-illness blood pressure readings from within last 3 years, as validated previously) [8, 10, 11] during vasopressor support in ICU. Pre-illness blood pressure will primarily be obtained from outpatient clinic records, including ambulatory blood pressure monitoring, general practitioner or specialist visits, pre-admission assessments, or echocardiography clinics. Where these records are unavailable, values from the observation charts of a previous hospitalisation within the last 48 h will be used. The pre-illness MAP will be targeted, within the range of 55–95 mmHg, for the duration of vasopressor therapy for up to a maximum of 5 days. The treating clinician can tailor these BP targets if required and as deemed suitable for evolving clinical state. The type of vasopressor that will be used is at the discretion of the treating clinician. If the total additional vasopressor dose required to achieve these individualised MAP targets exceeds 0.75 µg/kg/min (noradrenaline-equivalent [12]), or if in the opinion of the treating clinician the patient is unlikely to benefit or may suffer possible adverse effects, then the blood pressure targets may be adjusted in 5 mmHg steps from the prior level, until a clinically acceptable MAP target is identified.

### Criteria for discontinuing or modifying allocated interventions

Study intervention will cease after 5 days or earlier if a patient is considered well enough by the treating clinician for discharge out of ICU.

### Strategies to improve adherence to interventions

Protocol adherence for enrolled participants will be monitored regularly. Protocol deviation will be defined as failure to adjust dose of vasopressor agents while the MAP remained at least 6 mmHg above or below the set target for 4 consecutive hours, without a documented change of MAP target by the treating clinician. Monitor alarms may be adjusted to prompt appropriate titration of vasopressors or inotropes to maintain target MAP. Study posters or cards (Figure S1) will be provided to participating sites. Cards will show an easy-to-follow algorithm for study-related procedures for each group. Site monitoring will be performed to ensure protocol adherence. The site principal investigator will take primary responsibility for training local staff using study tools provided by the coordinating centre.

### Relevant concomitant care permitted or prohibited during the trial

There are no restrictions to concomitant therapies provided to patients in the study. Participating sites will be requested to adhere to best practice guidelines, regardless of assigned blood pressure targets, in relation to other potentially confounding co-interventions such as fluid management, blood transfusion, sedation interruption, ventilator weaning, nutrition, or use of steroids. Co-enrolment will not be permitted for any other interventional study that is directly related to blood pressure targets.

### Outcomes

The primary outcome is 14-day all-cause mortality. Mortality will be a binary variable, with mortality defined as a record of death within 14 days after randomisation.

Secondary outcomes (Table 3) are:90-day all-cause mortality: All-cause mortality from randomisation to day 90.Time to death through day 14: Time to death (hours) will be calculated as the difference between the date and time of death and the date and time of randomisation if death occurs within 14 days of randomisation. Where exact time of death is not available, time will be assumed as 12:00 on the date of death.Time to death through day 90: Time to death (days) will be calculated as the difference between the date of death and the date of randomisation.Major Adverse Kidney Event (MAKE-14): MAKE-14 is defined as a composite measure of death, new initiation of RRT, or doubling of serum creatinine from the premorbid level at day 14 [13, 14]. Individual components of MAKE-14 will also be reported. The premorbid serum creatinine level will be sourced as the latest available value from medical records within the last year before hospital admission or, if this value was unavailable, as the latest available value during the hospital stay at least 7 days before ICU admission. When neither of these are available, the premorbid serum creatinine will be estimated following the Kidney Disease: Improving Global Outcome (KDIGO) guidelines as described previously [15].Renal Replacement therapy (RRT) free days until day 28: Number of days from randomisation to day 28 where the participant is both alive and not dependent on RRT. Patients who die within 28 days will be assigned the worst score of − 1.

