### Participant timeline

A schematic table (Table 1) showing the schedule of enrolment, intervention and assessment in accordance with the SPIRIT guidance [18] is presented. Relevant characteristics of screened patients including date of screening and reason for exclusion will be recorded. Patient flow will be presented as a CONSORT diagram (Fig. 1).

**Table 1 Tab1:** Schedule of enrolment, intervention and assessments

Activity	Screening	Baseline info	Day 0–5	Day 6–14	Day 28	Day 90
Eligibility criteria evaluation	x					
Informed consent	x					
Demographics	x	x				
Randomisation		x				
Past medical history		x				
Use of nephrotoxic agents		x	x	x		
Vasopressor dose/use		x	x			
Peak serum creatinine		x	x	x	x	
MAP (recorded 4 hourly)		x	x			
Intervention period			x			
Safety outcomes			x	x	x	
Renal replacement therapy			x	x	x	
MAKE-14			x	x		
Mortality			x	x	x	x

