Serum lactate at randomisation, median [IQR], mmol/l		
Pre-illness serum creatinine, median [IQR], micromole/l		
Serum creatinine at randomisation, median [IQR], micromole/l		
Intravenous fluid given within 24 h prior to randomisation, median [IQR], ml		
Fluid balance at randomisation, median [IQR], ml		
Exposure to nephrotoxic agents within 72 h prior to randomisation, *n* (%)		
ACE inhibitor or angiotensin receptor blocker		
Intravenous contrast		
Non-steroidal anti-inflammatory drug		
Aminoglycoside		
Vancomycin		
Calcineurin inhibitor		
Gancyclovir		
Remdesivir		
Number of nephrotoxic agents within 72 h prior to randomisation, median per patient [IQR]		
Time from ICU admission to randomisation, median [IQR], h		
Time from T0^§^ to randomisation, mean (SD), h		

*IQR* interquartile range, *APACHE* Acute Physiology and Chronic Health Evaluation, *BP* blood pressure,

*MAP* mean arterial pressure, *ACE* angiotensin converting enzyme

^§^ T0—Time-point, when vasopressor or inotrope support was initiated

**Table 3 Tab3:** Exposure variables and other process of care measures

Characteristics	Standard MAP (*n* = xxx)	Individualised MAP (*n* = xxx)
Target MAP on randomisation, median [IQR], mmHg		
MAP-deficit^*^ (time-weighted average), median [IQR], %		
Percentage of time spent with > 20% MAP-deficit^**χ**^, median [IQR], %		
Achieved MAP ^#^ during the treatment period, median [IQR], mmHg		
Time-weighted average vasopressor dose (noradrenaline-equivalent), median [IQR], mcg/kg/min		
Time from randomisation to cessation of vasopressors, median [IQR], h		
Exposure to nephrotoxic agents within 14 days after randomisation, *n* (%)		
ACE inhibitor or Angiotensin receptor blocker		
Intravenous contrast		
Non-steroidal anti-inflammatory drug		
Aminoglycoside		
Vancomycin		
Calcineurin inhibitor		
Gancyclovir		
Remdesivir		
Number of nephrotoxic agents within 14 days after randomisation, median per patient [IQR]		
Exposure to blood transfusion within 5 days after randomisation, *n* (%)		
ICU length of stay post randomisation among survivors, median [IQR], days		
Hospital length of stay post randomisation among survivors, median [IQR], days		

*IQR* interquartile range, *MAP* mean arterial pressure, mmHg

^*****^ MAP-deficit = [(pre-illness MAP − achieved MAP)/pre-illness MAP] × 100, using positive incremental area-under-the-curve of MAP-deficit during vasopressor therapy

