### Primary outcome

Effect estimates for 14-day all-cause mortality will be derived from multivariable logistic mixed effects models with a random intercept for site (assumed normally distributed on the logit scale, with a constant variance) to account for clustering within sites and fixed effects for treatment group, time between T0 (initiation of vasopressor therapy) and randomisation, APACHE III score at randomisation, noradrenaline-equivalent dose at randomisation and type of shock (Table 4). A two-sided *P*-value for the effect of treatment will be obtained from this model and values < 0.05 will be considered statistically significant. The effect estimates of interest will be the relative risk and risk difference (individualised care versus standard care). The relative risk estimate will be obtained as a ratio of the mean for each group of the individual predicted probabilities obtained from the logistic regression model. Differences of these means will be the risk difference. Bootstrapping, using 10,000 iterations, will be used to calculate 95% confidence intervals.

**Table 4 Tab4:** Outcome measures

	Standard MAP (*n* = xxx)	Individualised MAP (*n* = xxx)	Adjusted^*^ relative risk (95% CI)	Adjusted^*^ risk difference (95% CI)	*P* value
Day 14 all-cause mortality, *n* (%)					
Major Adverse Kidney Event^δ^ within 14 days of randomisation, *n* (%)					
- New requirement for RRT					
- Doubling of creatinine					
RRT- free days^#^ by day 28, *n* (%)					
Day 90 all-cause mortality, *n* (%)					

*RRT* renal replacement therapy

^*^ The model included random intercepts for sites and fixed effects for treatment group, the time between T0 (initiation of vasopressor therapy) and randomisation, APACHE III score at randomisation, vasopressor dose at randomisation and type of shock

^**δ**^ Major adverse kidney event (MAKE)−14 was a composite outcome of death, or new renal replacement therapy during the first 14 days, or doubling of serum creatinine from pre-illness level on day 14 or on day of discharge from ICU, whichever was earlier

^#^ Patients who died were assigned the worst score of − 1

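### The creatinine component of MAKE-14 has two conflicting definitions, and the one in the Table 4 footnote lets the measurement day depend on ICU discharge

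*Protocol article*

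**What the plan says.** The Outcomes section of the protocol article defines MAKE-14 as a composite of death, new RRT, or "doubling of serum creatinine from the premorbid level at day 14". It adds that the components will also be reported individually.

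Table 4, under Primary outcome, labels the row as events "within 14 days of randomisation". Its footnote describes "a composite outcome of death, or new renal replacement therapy during the first 14 days", and then adds "doubling of serum creatinine from pre-illness level on day 14 or on day of discharge from ICU, whichever was earlier".

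Both texts are current, and neither refers to the other. The abstract lists the endpoint first among the secondaries ("Secondary endpoints are major adverse kidney events by day 14, all-cause 90-day mortality"). The hypothesis pairs it with mortality ("which may help reduce the risk of 14-day mortality and major adverse kidney events in ICU"). Under Secondary outcomes, MAKE-14 is analysed with the same model as 14-day mortality.

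Table 1 has a MAKE-14 row ticked for Day 0–5 and Day 6–14, which fixes no measurement day. It also has a separate row for "Peak serum creatinine".

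**The concern.** There are two problems, and settling the first does not settle the second.

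**Ambiguity.** A patient discharged alive from ICU on day 5, with no RRT, is judged on day-14 creatinine under one rule and on day-5 creatinine under the other. A patient whose creatinine had doubled on day 5 and recovered by day 14 is an event under the footnote and a non-event under the Outcomes text. If the choice is left until after unblinding, it can be made with knowledge of the results.

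**Dependence on ICU stay.** Under the footnote, the day of measurement is itself a post-randomisation variable. The introduction says that individualised targets may increase vasopressor use. Table 3 compares time to vasopressor cessation and ICU stay by arm. Readiness for ICU discharge is the treating clinician's judgement (Criteria for discontinuing or modifying allocated interventions), and those clinicians are unblinded (Blinding). If the strategy lengthens or shortens ICU stay, the arms are compared at different points of the creatinine course.

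**Working it through.** **1. The plan's own figure.** The documents give no event rate, power or sample size for MAKE-14. The only sample size is for 14-day mortality: 20% v 14%, two-sided alpha 0.05, 80% power, 2.5% attrition.

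- Per arm: [1.960 × √(2 × 0.17 × 0.83) + 0.842 × √(0.20 × 0.80 + 0.14 × 0.86)]² / 0.06² = 615 after rounding up.
- Total: 1230; 1230 / 0.975 = 1262, against 1260 stated.

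The figure reproduces, and this point does not affect it.

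**2. The two rules side by side.**

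| Patient | Outcomes text | Table 4 footnote |
|---|---|---|
| Dies, or starts RRT, within 14 days | Event | Event |
| Alive, no RRT, in ICU at day 14 | Day-14 creatinine | Day-14 creatinine |
| Alive, no RRT, left ICU before day 14 | Day-14 creatinine | Creatinine on day of ICU discharge |

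The conflict is confined to the third row.

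**3. How large could it be? An illustration on assumptions only.** The documents give no ICU stay or creatinine course. Assume, for survivors without RRT and identically in both arms:

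- ratio to premorbid at randomisation, P: log-normal, median 1.6, log-SD 0.5;
- recovery r(t) = 1 + (P − 1) × 2^(−t/h), with half-life h of 3, 5 or 8 days;
- ICU stay: log-normal, median 4 days, log-SD 0.7.

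Doubling at day t requires P ≥ 1 + 2^(t/h). By hand for h = 5:

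- Day 4: P ≥ 1 + 1.741 = 2.741; z = (ln 2.741 − ln 1.6) / 0.5 = 1.08; 14.1% doubled.
- Day 5: P ≥ 3; z = 1.26; 10.4%.
- Day 14: P ≥ 7.964; z = 3.21; 0.07%.

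Averaged over the ICU-stay distribution by simulation (2 million patients):

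| h (days) | Day-14 rule | Footnote rule | Footnote rule, one extra ICU day | Difference with no kidney effect |
|---|---|---|---|---|
| 3 | 0.0% | 7.8% | 4.6% | 3.2 points |
| 5 | 0.1% | 13.6% | 10.4% | 3.2 points |
| 8 | 2.3% | 19.0% | 16.4% | about 2.5 points |

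A half-day shift gives about 1.3 to 1.7 points, and two days about 5 to 6. The day-14 rule gives no difference in any of these cases.

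**4. Dilution in the composite.** Deaths and RRT starts are already events, so the shift applies only to the remaining patients. With the plan's 20% control mortality and no RRT at all, the composite moves by at most 0.80 × 2.5 to 0.80 × 3.2 = 2.0 to 2.6 points. With an assumed 12% starting RRT, unrelated to creatinine, it is 0.68 × 2.5 to 0.68 × 3.2 = 1.7 to 2.2.

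**5. Direction.** Now let creatinine rise linearly to a peak at day 2 (median ratio 1.7, log-SD 0.45) and then recover with the same half-lives, with exponential ICU stay of mean 6 days. One extra ICU day then gives more doubling in the longer-stay arm: 10.8% to 12.3%, 14.0% to 16.2%, and 17.6% to 20.3%, which is 1.5 to 2.7 points the other way. The direction is therefore not determined.

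**The case against.** The strongest reply is that the text conflict is a drafting slip: the Outcomes wording may be shorthand for the fuller footnote. The article does not say so. If it is so, the ambiguity goes but the dependence on ICU discharge stays.

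The other side is right on several points, and they limit the finding:

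- **Premise.** The article says vasopressor use may rise. It does not say ICU stay will change. A uniform one-day delay is an assumption, and the size and sign of any bias are unknown.
- **Scope.** Only one component of a secondary outcome is exposed. The primary outcome, its model and the sample size are untouched.
- **Measurement.** Creatinine is a laboratory value and the analyst is blinded. That protects the reading, but not the choice of day.

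A reader might also infer a third definition based on peak creatinine, since the schedule lists no day-14 or ICU-discharge value. The documents do not support this. Table 1 has its own MAKE-14 row, and Objectives names peak increase in creatinine as a separate secondary objective, so it should neither define MAKE-14 nor be demoted.

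Nor is it an error that the MAKE-14 model omits baseline creatinine, although Table 2 collects it ("Serum creatinine at randomisation, median [IQR], micromole/l"). A randomised comparison is not biased by that omission; adding it is a modest, optional gain in precision.

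**Conclusion.** The point holds in two parts. The two current definitions conflict for every patient who leaves ICU alive before day 14 without RRT. The footnote version also makes the assessment day a post-randomisation variable that the intervention could plausibly change.

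The documents fix no magnitude. The 2.5 to 3 points per extra ICU day rest wholly on assumed recovery curves, ICU stays and a uniform shift. They concern the creatinine component, shrink in the composite, and can change sign. It would be wrong to conclude that the plan builds in a kidney benefit, or that a primary or designated key endpoint is compromised. What can be said is that one rule is free of this artefact and the other is not, and that the plan currently contains both.

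**What to change.** Before unblinding, put one definition in the Outcomes section, the Table 4 footnote and the data collected:

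- Creatinine at least twice the premorbid value at day 14, using the value nearest to day 14 or, for patients already out of hospital, the last available value on or before day 14. Do not tie it to ICU discharge.
- State that this fallback still depends partly on hospital stay. In the step 5 set-up, with an assumed exponential ward stay of mean 5 days and creatinine either at its peak from randomisation or rising to day 2, one extra day carried through to hospital discharge still shifts doubling by roughly 1 to 2 points. The fallback is needed because outcomes are analysed as complete cases, and the best–worst imputation covers mortality only.
- Report a sensitivity analysis under the ICU-discharge rule.
- Keep peak increase in creatinine as the separate secondary objective.
- Optionally, adjust the MAKE-14 model for creatinine at randomisation relative to premorbid.

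Cost: a ward creatinine must be looked up for patients who leave ICU before day 14, across up to 35 sites. The trial is already recruiting, so a minor protocol variation with the relevant approvals is also needed. The primary analysis does not change.
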